### Effectiveness assessment

After randomization of each facility, standard training or MP-ICT training will be conducted. Evaluations will include a baseline assessment of available equipment and supplies for neonatal resuscitation, immediately after enrolment and before training. To determine the duration of the effects of the intervention, the proposed outcome indicators will be evaluated six months after the training. The primary and secondary outcomes will be assessed intrapartum (within 5 minutes after birth) and postpartum (at 24 hours and 7 days, to know the outcome of the infant). The assessments will be based on an observation sheet (see
Supplementary File 3), in which trained research assistants (registered nurses or equivalent local personnel) will record the activities conducted during the delivery and the birth, and the results of the neonatal resuscitation. The observation of performance in neonatal resuscitation will also be recorded randomly through videos, to verify the validity of the data collected by the research assistant. The videos will be reviewed by the field monitor and by one of the investigators. In order to comply with confidentiality requirements, the videos will be deleted after verification of information.

### Statistical analysis

An intention to treat analysis will be performed, including all clusters as they were initially assigned, including premature withdrawals. Additionally, a per-protocol analysis will be carried out, where only clusters that have completed the study protocol will be considered. The primary outcome will be compared in each arm using Chi-square test if the variable of distribution is normal, or alternatively through the Fisher’s exact test. Secondary outcomes will be compared using the Student’s t-test or the Kruskal-Wallis test. For supplementary oxygen use, the Chi-square test or Fisher’s exact test will be used.

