## Abstract

**Background**: About 10% of all newborns may have difficulty breathing and require support by trained personnel. In Peru, 90% of deliveries occur in health facilities. However, there is not a national neonatal resuscitation and certification program for the public health sector. In addition, the Andes and the Amazon regions concentrate large rural remote areas, which further limit the implementation of training programs and the accomplishment of continuous certification. Neonatal resuscitation training through the use of information, communication and technology (ICT) tools running on computers, tablets or mobile phones, may overcome such limitations. This strategy allows online and offline access to educational resources, paving the way to more frequent and efficient training and certification processes.

**Objective**: To evaluate the effects of a neonatal resuscitation training and certification program that uses a multi-platform ICT (MP-ICT) strategy on neonatal health care in remote areas.

**Methods**: We propose to conduct the study through a cluster-randomized trial, where the study and analysis unit is the health care facility. Eligible facilities will include primary and secondary health care level facilities that are located in provinces with neonatal mortality rates higher than 15 per 1,000 live births. We will compare the proportion of newborns with a heart rate ≥100 beats per minute at two minutes after birth in health care facilities that receive MP-ICT training and certification implementation, with those that receive standard training and certification.

**Discussion**: We expect that the intervention will be shown as more effective than the current standard of care. We are prepared to include it within a national neonatal resuscitation training and certification program to be implemented at national scale together with policymakers and other key stakeholders.

**Trial registration**: ClinicalTrials.gov Nº NCT03210194

**Status of the study**: This study is enrolling participants by invitation only.

Study protocol version 1.1 – March 31st, 2017

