### Study design

The proposed study design is a randomized cluster trial. The units of study and analysis will be twelve health facilities from Ayacucho and Cusco departments. Each health facility will be a cluster. Clusters will be randomly assigned either to the MP-ICT course and certification package (intervention) or to the standard training and certification package (control). Additional details are shown in
Table 1.

**Table 1. T1:** Schedule of enrolment, interventions, assessments and final report: RCPNEOPERU Project.

	STUDY PERIOD									
	Project Management		Allocation	Post-allocation		Pause	Assessments			Close-out
BIMESTER	*B _-2_*	*B _-1_*	*0*	*B _3_*	*B _4_*	*B _5_*	*B _6_*	*B _7_*	*B _8_*	*B _9_*
	*2017-04* *2017-05*	*2017-06* *2017-07*		*2017-08* *2017-09*	*2017-10* *2017-11*	*2017-12* *2018-01*	*2018-02* *2018-03*	*2018-04* *2018-05*	*2018-06* *2018-07*	*2018-08* *2018-09*

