### Sample size

We must emphasize that our study will be conducted at a pilot scale and thus we considered the minimum sample size for such study level. Assuming the occurrence of about 4,000 births during a period of 6 months of filed study observation, we aim at discriminating a 4% difference in the proportion of newborns with heart rate equal or greater than 100 beats per minute at two minutes of life between the intervention and the control group
^18^. We would require 12 clusters (health facilities) divided in two arms, with six facilities allocated to each arm, and with an average of 334 deliveries per facility during the observation period. The proposed power of the study is 80% and the acceptable alpha error is 5%. The percentage for heart rate >100 bpm at two minutes of life during suitable resuscitation using self-inflated bag is 90%
^21^, and it is the expected value for the intervention group. For the control group, at least 4 percentage points below the value achieved in the intervention group is expected (i.e. no more than 86%).

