### Outcomes

Our primary outcome is the percentage of infants with heart rate equal or greater than 100 per minute at two minutes of life. This outcome is an adequate proxy for effective response to neonatal resuscitation measures in the delivery room
^20,
21,
23^.

The secondary outcomes are described in our secondary objectives.

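### The primary test is an ordinary Chi-square or Fisher test although matched facilities are randomised, so the 5% error rate is not held for any between-facility correlation that matching leaves

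*Protocol article*

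**What the plan says.** The Study design section makes the facility the unit of randomisation ("Each health facility will be a cluster") and of analysis: "The units of study and analysis will be twelve health facilities from Ayacucho and Cusco departments". The Abstract agrees: "where the study and analysis unit is the health care facility". The Randomization section adds that facilities are matched on staff mix and on equipment and supplies, then allocated at random once paired.

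The outcome is scored per infant: "Our primary outcome is the percentage of infants with heart rate equal or greater than 100 per minute at two minutes of life".

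The Statistical analysis section then fixes the test: "The primary outcome will be compared in each arm using Chi-square test if the variable of distribution is normal". If that condition fails, the fallback is Fisher's exact test. The section names no facility-level summary, random effect, GEE, robust variance or design-effect correction, and makes no use of the pairs. Secondary outcomes are assigned Student's t-test or Kruskal-Wallis, and supplemental oxygen the Chi-square or Fisher test. The only mention of clusters there defines the intention-to-treat and per-protocol sets.

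The Sample size section sets alpha at 5% and power at 80% for 90% against 86%, with six facilities per arm and an average of 334 deliveries per facility. It gives no ICC and no design effect.

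**The concern.** The named test fits neither level at which it could be run.

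- **Newborn level.** A Chi-square or Fisher test on about 4,000 births treats them as independent. Births in one facility share staff, equipment and training session, so the variance of the difference between arms is understated. This also contradicts the declared unit of analysis.
- **Facility level.** The data are twelve percentages, six per arm. A contingency-table test does not apply to them.

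The rule for choosing between the two tests does not help. A yes/no outcome is not normally distributed, so the condition cannot be checked. Fisher's test makes the same independence assumption as the Chi-square.

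At stake is the main claim. The Abstract and the Expected results section tie a positive result to a national programme. With six facilities per arm, a chance imbalance between facilities could be read as an effect of training.

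**Working it through.** **Inputs.** From the Sample size section: 6 facilities per arm, m = 334, so 2,004 births per arm and 12 × 334 = 4,008 in all; 90% against 86%; alpha 5% (two-sided assumed, as sidedness is not stated); power 80%. The ICC is not given, so a range is assumed.

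**1. The plan's own figure.** For independent births, the required number per arm is

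[1.96 × √(2 × 0.88 × 0.12) + 0.8416 × √(0.90 × 0.10 + 0.86 × 0.14)]² / 0.04² = 1,035,

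or 2,070 in total. The planned 4,008 is 1.94 times that, and would give 97.4% power without clustering. The stated size therefore does not follow from the stated inputs. If the excess is an unstated allowance for clustering, 1 + 333 × ICC = 1.94 gives an ICC of about 0.0028. That value is used below as one point of the range; the article does not state it.

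**2. Error rate of the unadjusted test, no gain from matching.** Design effect D = 1 + (334 − 1) × ICC. Actual two-sided error = 2 × [1 − Φ(1.96/√D)].

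| Assumed ICC | D | Actual error at nominal 5% |
|---|---|---|
| 0 | 1.00 | 5.0% |
| 0.001 | 1.33 | 9.0% |
| 0.0028 | 1.93 | 15.9% |
| 0.005 | 2.67 | 23.0% |
| 0.01 | 4.33 | 34.6% |
| 0.02 | 7.66 | 47.9% |

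Beta-binomial simulation (40,000 replicates per scenario) agrees to within about half a point. Fisher's test, with 3,000 replicates, rejects 14.2% of true nulls at ICC 0.0025 and 32.6% at 0.01.

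**3. With matching.** If a fraction f of the between-facility variance is shared within pairs, D becomes about 1 + 333 × ICC × (1 − f). The values of f are assumptions.

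| Assumed ICC | f = 0 | f = 0.5 | f = 0.8 |
|---|---|---|---|
| 0.0028 | 16% | 10.5% | 7% |
| 0.01 | 35% | 23% | 13% |

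The error stays above 5% unless matching removes all of the between-facility variance.

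**4. A valid alternative.** An unpaired t-test on the twelve facility proportions (10 df) held the error at 4.7% to 5.0% in simulation for ICCs from 0 to 0.05. Its power for 90% against 86%, with standard error √[(0.90 × 0.10 + 0.86 × 0.14)/2,004 × D], is:

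| Assumed ICC | Power, t-test on 10 df |
|---|---|
| 0.001 | 86% |
| 0.0028 | about 71% |
| 0.005 | 58% |
| 0.01 | 40% |

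**5. Exact permutation within pairs.** Six pairs give 2⁶ = 64 allocations. The smallest two-sided p is 2/64 = 0.031 and the next is 4/64 = 0.0625, so the test rejects at 5% only when all six pairs favour the same arm. Simulated power with no gain from matching is about 68% at ICC 0, 42% at 0.0028 and 21% at 0.01.

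**The case against.** **The size of the inflation is not known.** This stands. The article gives no ICC, and the matching could reduce the error appreciably, as step 3 shows. A reader might infer that the trial's false-positive rate is, say, 35%. The documents do not support any single figure. They support only the direction: above 5% for any positive correlation that matching does not remove.

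**The planned confidence interval is too narrow.** A reader might infer this too. The article announces no confidence interval, so there is no such plan to fault. The remark is conditional: an interval built on the same independence assumption would need widening by √D, which is 1.15 at ICC 0.001 and 2.08 at 0.01, before allowing for t on few degrees of freedom.

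**The text never says the test is run on pooled newborns.** True. That is an inference, and the declared unit of analysis points the other way. But the facility-level reading gives no workable Chi-square or Fisher test, so the sentence fails either way.

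**Details may sit in an analysis plan that is not shown.** Detail may, but the article names a specific primary test, and that test does not fit the design. Keeping all clusters in the intention-to-treat set settles who is analysed, not how the variance is computed. The pilot label in the Sample size section does not change this, since alpha is set at 5% and a national programme is expected to follow.

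**Conclusion.** The point holds and must be fixed. The primary test named in the article conflicts with the randomisation and with the declared unit of analysis, and the rule for choosing it cannot be applied to a binary outcome. The 5% error rate is not held if any between-facility correlation remains after matching. For 6 against 6 facilities of 334 births and no gain from matching, the error is about 9% at ICC 0.001, rising to about 35% at 0.01. At the ICC that the planned 4,008 births would imply, it is about 16%. These figures rest on assumed ICCs, equal cluster sizes and a two-sided test; effective matching would lower them.

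**What to change.** Replace the primary-test sentence with one pre-specified cluster-level analysis. Suitable choices are:

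- a t-based comparison of the facility proportions (10 df unpaired, 5 df if paired); or
- a mixed model or GEE with facility as cluster, a small-sample correction and account taken of the matching.

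Report the risk difference with a cluster-adjusted 95% confidence interval, and report the ICC. If an exact permutation test within the six pairs is considered, state that its smallest two-sided p is 0.031 and that its power is therefore low.

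Delete the normality condition. Apply the same cluster-level approach to every infant-level secondary outcome, including those now assigned Student's t-test or Kruskal-Wallis, and not only to supplemental oxygen.

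**Cost.** No new data are needed, but the change is more than one of wording. The valid analysis may not deliver the 80% power in the Sample size section: by step 4, an unpaired facility-level t-test falls below 80% by ICC 0.0028. A paired test has fewer degrees of freedom and gains only if the matching works. The power should be restated under an explicit ICC. This is no reason to keep the unadjusted test, because its apparent extra power comes from an error rate above 5%.

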## Introduction

### Background

Approximately 10% of newborns may have difficulty breathing at birth and require urgent support from trained personnel
^1^. The first 60 seconds of life in those conditions require immediate and effective interventions to help infants survive
^2^. Unfortunately, some newborns in low- and middle-income countries do not have access to appropriately trained personnel, making asphyxia one of the leading causes of neonatal death in those settings
^3^.

In Peru, about 550,000 births occur per year (Peruvian Institute for Statistics and Informatics 2015;
https://www.inei.gob.pe), and this means that approximately 6 newborns each hour may require respiratory support at birth. Problems in training health workers for adequate support of newborns is aggravated by a high turnover rate of personnel, particularly in small cities and rural areas, which hampers regular conduction of local training programs, even if they are perceived as a positive incentive
^4^. Peru is a high-middle-income country that has made significant progress in reducing neonatal and infant mortality in the last decade, despite inequities in access to health services, especially in rural areas of the Amazon and the Andes
^5,
6^. In the years 2011–2012, the Peruvian neonatal mortality rate was estimated at 12.8 per thousand live births
^7^, with an estimated 20 per thousand live births for Pasco and Cusco regions, 15 for Ayacucho and Amazonas, 12 for Huancavelica and 8 for Lima
^8^. From 2000 to 2013, neonatal mortality in Peru fell by 51% from 16.2 deaths per 1000 livebirths to 8.0
^9^.

The Neonatal Resuscitation Program (NRP) from the American Academy of Pediatrics, includes evidence-based clinical guidelines and was designed to train health care providers and instructors in hospital settings. The NRP is a paid course that has 2 components, an online component (internet-dependent) and a practice/evaluation component
^1,
10^. A variant of the NRP program is the Helping Babies Breath (HBB) program, which was designed to provide neonatal resuscitation training in resource-poor settings. The HBB has shown to reduce neonatal mortality and it is proposed as a successful global intervention
^11^. However, the greatest limitation of these programs is the need for recurrent training with a frequency of less than 12 months to maintain the acquired skills and knowledge
^12^.

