### Secondary objectives

To assess intervention and control efficacy in selected health facilities, in order to compare: 1) Time to start positive pressure ventilation after birth; 2) Time to achieve heart rate greater or equal than 100 per minute; 3) Apgar at 1 minute and at 5 minutes; 4) Use of supplemental oxygen after 10 minutes of life; 5) Inspiratory oxygen fraction needed at 30 minutes after birth; 6) Mortality rate during the first 7 days of life; 7) Number of referrals to health facilities with greater resolution capacity during the first 7 days of life; 8) Number of certified health professionals as providers.; and 9) Number of certified health professionals as instructors.

The efficacy of the evaluation will be evaluated at 6 months after the intervention.

Status of the study: This study is ongoing.

Study protocol version 1.0 – March 31th, 2017.

Trial registration data can be found in
Supplementary File 1.

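### Secondary outcomes are sent to two-sample t-tests or Kruskal-Wallis tests with no allowance for the 12 matched facilities, and the rule does not fit the two time outcomes

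*Protocol article*

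**What the plan says.** The Statistical analysis section of the protocol article gives one rule: "Secondary outcomes will be compared using the Student’s t-test or the Kruskal-Wallis test". It makes one exception: "For supplementary oxygen use, the Chi-square test or Fisher’s exact test will be used". It does not say which outcome gets which test, whether the test runs on infants or facilities, or how pairs enter.

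The Secondary objectives therefore place under the rule "Mortality rate during the first 7 days of life", "Number of referrals to health facilities with greater resolution capacity during the first 7 days of life", "Time to start positive pressure ventilation after birth" and "Time to achieve heart rate greater or equal than 100 per minute", besides Apgar, inspired oxygen fraction and the two counts of certified staff.

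The Study design section randomises twelve facilities and names the facility as what is studied and analysed. The Randomization section matches facilities on staffing and equipment before allocating them. On timing, the Effectiveness assessment section says: "The primary and secondary outcomes will be assessed intrapartum (within 5 minutes after birth) and postpartum".

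**The concern.** Infants born in one facility share staff, equipment and training, so their outcomes are correlated. A two-sample test that counts infants as independent understates the variance and finds differences too often.

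The paragraph is also inconsistent within itself. Oxygen use and 7-day death are both yes/no per infant, but only oxygen gets a test for proportions.

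The two times raise a separate problem, because some infants have no value. An infant who dies or stays below 100 while watched has no time to 100. An infant who is not ventilated has no ventilation time. Without a rule for these infants, the comparison may be between groups that randomisation did not form.

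**Working it through.** **Inputs.** From the Sample size section: 6 facilities per arm, 334 births each, so 6 × 334 = 2,004 per arm; 90% vs 86%; power 80%; alpha 5%. From the Background: about 10% of newborns need breathing support. The documents give no ICC, so a range is assumed.

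**1. The plan's own figure.** For two independent proportions, two-sided:

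n = [1.960·√(2 × 0.88 × 0.12) + 0.842·√(0.90 × 0.10 + 0.86 × 0.14)]² / 0.04² = (0.901 + 0.386)² / 0.0016 ≈ 1,035 per arm.

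The stated 2,004 is not reproduced without clustering. It matches 80% power if the design effect is 2,004 / 1,035 = 1.94, that is, an ICC of (1.94 − 1) / 333 ≈ 0.0028. This is a useful low anchor, although the article does not state it.

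**2. False-positive rate of an infant-level test.** The design effect is DE = 1 + 333 × ICC. The true size is approximately 2 × [1 − Φ(1.96 / √DE)]. The simulation used 6 vs 6 facilities of 334, beta-binomial outcomes with 2% events, no true effect, no matching and 20,000 runs:

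| ICC (assumed) | DE | Formula | Simulated, infant level | Simulated, t-test on 12 facility rates |
|---|---|---|---|---|
| 0 | 1.00 | 5.0% | 5.1% | 5.1% |
| 0.001 | 1.33 | 9.0% | 8.9% | 4.9% |
| 0.0028 | 1.93 | 15.9% | 15.6% | 4.9% |
| 0.01 | 4.33 | 34.6% | 34.6% | 4.3% |
| 0.02 | 7.66 | 47.9% | 47.0% | 4.0% |

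The infant-level t-test and chi-square gave the same rates. At 0.8% and 5% events the results are close to these.

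**3. Does the choice of test matter for death or referral?** For 24 vs 40 events among 2,004 per arm, p = 0.0438 by t-test, Kruskal-Wallis and uncorrected chi-square alike, and 0.0579 by Fisher. The first three agreed to four decimals in all six examples tried. Moving these outcomes to chi-square would therefore leave the error rates in step 2 unchanged.

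**4. Time to heart rate of 100 or more.** This is an illustration with assumed inputs: 2,004 independent infants per arm, the same lognormal times among achievers in both arms (log-scale SD 0.4), and 400 runs.

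- Never reach 100 in 2% vs 6%: a t-test on achievers only rejects in about 6% of runs; Kruskal-Wallis with non-achievers ranked worst rejects in about 58%.
- 2% vs 4%: about 5% and 19%.
- 2% vs 2%: 3% and 4.5%, as expected under no difference.

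An achievers-only comparison would miss a real difference in failures.

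**5. Time to ventilation.** If about 10% of births are ventilated, a facility contributes about 33 times. The clustering penalty is then smaller: DE = 1 + 32.4 × 0.0028 = 1.09 and 1 + 32.4 × 0.01 = 1.32, for sizes of about 6% and 9% by the formula in step 2. The main problem here is selection. Staff decide whom to ventilate after allocation, and the training is meant to change what staff do.

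**The case against.** The strongest reply is that the facility is the declared unit of analysis. Mortality is then a facility rate, referrals a facility count, and a t-test or rank test on 12 values is a recognised cluster-level method; step 2 shows that it holds its size. This would be a full answer if the Statistical analysis section said so. It does not, and the chi-square and Fisher tests beside the rule compare counts of infants. The infant-level reading is therefore the natural one, though it is not written down.

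It is also fair that these are secondary outcomes in a study described as pilot scale, and that detailed handling of unreached times may sit in an analysis plan not shown. But the article has already fixed the tests, and that choice can be judged as it stands.

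Four stronger readings are tempting and not supported:

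- **That the plan drops infants who failed.** No exclusion or imputation rule is written, and Kruskal-Wallis, which the plan allows, can rank non-achievers worst.
- **That the 10% vs 14% not at target at two minutes are lost times.** An infant who reaches 100 at three or four minutes has an observed, longer time. The article gives no figure for infants who never reach it.
- **That infants without a ventilation time are failures.** Given "Approximately 10% of newborns may have difficulty breathing at birth and require urgent support from trained personnel", most of them did not need ventilation.
- **That a t-test is wrong for death because death is binary.** Step 3 shows the same p-value as uncorrected chi-square. The harm comes from ignored clustering.

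**Conclusion.** The point holds in this form. The rule makes no allowance for facility or pair. Applied to infants, its nominal 5% becomes about 16% at ICC 0.0028 and about 35% at ICC 0.01 for outcomes measured on all births, and less for ventilation time. These figures rest on assumed ICCs, equal facilities of 334 births, and the infant-level reading.

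For time to heart rate of 100 or more, the named t-test cannot include infants who never reach it without an invented value. Leaving them out could hide a real difference; how large that effect would be here is unknown, because the failure shares in step 4 are assumptions. Ventilation time among ventilated infants is not protected by randomisation.

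**What to change.** Replace the blanket sentence with a rule by outcome type, and state the level of analysis.

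- **All secondary outcomes:** use facility-level summaries compared within pairs, or a cluster- and pair-adjusted model with a small-sample correction. With 6 pairs, an exact paired permutation test has 2⁶ = 64 allocations, so its smallest two-sided p is 2/64 = 0.031.
- **7-day death, referral and oxygen use:** risk differences with confidence intervals.
- **Time to heart rate of 100 or more:** time-to-event, censored at the end of observation, with infants who die below 100 counted as not achieved to that point; or ranks with non-achievers ranked worst.
- **Ventilation:** report the proportion of all births ventilated by a prespecified time, and label the time among ventilated infants as descriptive. All births is the safer denominator, because the article does not say that breathing status at birth is recorded and the observation sheet is not shown.
- **Apgar, inspired oxygen fraction and certification counts:** facility means, mean ranks or counts.

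The cost is analysis wording. Intervals widen relative to infant-level ones by about √1.93 = 1.39 at ICC 0.0028 and √4.33 = 2.08 at ICC 0.01, before the small-sample correction. That width reflects uncertainty that the infant-level tests leave out.
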